### Plans for assessment and collection of outcomes {18a}

See main heading “Data collection and management”.

### Plans to promote participant retention and complete follow-up {18b}

N/A, patient retention is secured through hospital admission, and long-term follow-up data are dependent on visits at the outpatient clinic as part of standard care.

### Data management {19}

See main heading “Data collection and management”.

### Confidentiality {27}

See main heading “Data collection and management”.

### Plans for collection, laboratory evaluation and storage of biological specimens for genetic or molecular analysis in this trial/future use {33}

See main heading “Data collection and management”.

## Statistical methods

### Statistical methods for primary and secondary outcomes {20a}

Analyses for both co-primary outcomes will be performed using the intention-to-treat principle and additionally using the per-protocol principle for the co-primary non-inferiority outcome to evaluate consistency of both analysis approaches compliant with recommendations for non-inferiority analyses [25]. The absolute between-RCT-groups difference in the co-primary non-inferiority outcome (incidence of culture-proven EOS) (intervention—control) with its one-sided 95% confidence interval (CI) will be calculated. When the upper limit of this one-sided 95% CI is below 2%, non-inferiority can be claimed. The between-RCT-groups difference in proportions of the co-primary superiority outcome (unnecessary antibiotics administration) will be studied under a common superiority hypothesis and expressed as a 2-sided 95% CI and analyzed using Fisher’s exact test and mixed effects modeling with site as a random effect and GA as fixed factor (2-sided *p* < 0.05 considered statistically significant). Analyses of secondary outcomes will be performed according to the intention-to-treat principle using common two-tailed hypothesis tests with alpha equal to 0.05 and using two-sided 95% CIs. Because the analyses of the secondary outcomes are considered exploratory, no correction for type I error will be made. Differences between groups in continuous variables will be analyzed with Student’s *t*-test or, if continuous data is not normally distributed, the Mann–Whitney *U* test will be used. Categorical variables will be compared with the chi-squared test or Fisher’s exact test, as appropriate. Furthermore, mixed effects modeling will be performed with site as a random effect and including randomization stratification factors as appropriate.

The observational part of the study will focus on diagnostic accuracy analysis of presepsin, such as sensitivity, specificity, positive predictive value, negative predictive value, and receiver operating characteristic curves with optimal cut-off values per subgroup.

A detailed statistical analysis plan comprising all study outcomes will be completed before database lock and published separately.

### Interim analyses {21b}

An interim analysis is planned when half (50%) of the included patients have completed follow-up up till discharge home and will be performed by an independent statistician of the Data Monitoring Committee (DMC). Additional reviews will be conducted at the DMCs request. The DMC will make their final recommendations regarding the results of interim data analyses and may recommend early trial termination based on unanticipated safety concerns. The justifications for a recommendation to terminate the study prematurely due to clear harm will be based on data showing a notably increased (serious) adverse events in the intervention group. The primary focus of the interim analysis is a safety analysis evaluating the overall mortality during hospital admission in both RCT groups. The other safety outcomes are supportive safety data.

Halfway the study (i.e. when the first 450 included participants have completed follow up for their hospital admission), recommendations for stopping for overall mortality will be based on the following pre-specified formal stopping rule. The overall mortality rate in infants born below 32 weeks GA is estimated ~ 10% (based on data of the years 2019–2022 of the national registration program “Perined”). Assuming an incidence of mortality of 10% in the control group, if the incidence of mortality in the intervention group is at least 50% higher relatively (i.e. > 15%, relative risk > 1.5), this will be considered a warning sign for a safety concern and a justification for recommendation to stop the study prematurely. If this situation occurs, further inspection of the results will be incorporated in the decision whether or not to stop the study prematurely. This includes inspection of the intervention group to determine whether the excess mortality can be attributed to the presepsin-low group (not started with antibiotics) and/or the presepsin-high group (started with antibiotics). Also the relation of the other safety outcomes with the study intervention, and the overall study conduct will be taken into account by the DSMB to decide whether the trial can be continued unchanged, needs closer monitoring, or should be stopped.

The DSMB may also recommend cessation of the trial if it is unable to successfully recruit participants, encounters improper data handling, or is not able to successfully implement study protocols. A formal interim analysis for efficacy (inferential testing) will not be conducted.

### Methods for additional analyses (e.g. subgroup analyses) {20b}

Subgroup analyses are planned for GA 24–28 weeks versus 28–32 weeks and SGA patients. Subgroup analyses and any other additional analyses will be further specified in the statistical analysis plan, which will be completed before database lock and published separately. A prospective economic evaluation will be performed in line with the randomized part of the study, providing insight into the value of the addition of a presepsin-guided step to the Dutch EOS guideline by reducing unnecessary antibiotic exposure directly after birth in preterm infants born < 32 weeks GA and at moderate risk of EOS. The executed cost-effectiveness analysis will reflect the health care costs and direct and indirect consequences expressing the benefits of the presepsin-guided step based on current practice (Dutch EOS guideline) compared to the new strategy.

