**Methods:**

The PRESAFE trial is a multicentre, randomized controlled trial (RCT), including a concurrent observational study. Presepsin levels are determined from umbilical cord blood or during the first regular blood draw in all infants born < 32 weeks gestation. Infants who qualify for empirical antibiotics according to the Dutch EOS guideline are categorized as moderate or high risk for EOS based on prespecified high-risk criteria. Infants not qualifying for empirical antibiotics are categorized as low risk. Preterm infants with a moderate risk for EOS are randomized 1:1 into an intervention arm and a comparator arm. In infants allocated to the intervention arm, empirical antibiotics will only be started above a prespecified presepsin level of ≥ 645 pg/ml. In the comparator arm, infants will be treated according to the standard of care following the Dutch EOS guideline, equivalent to starting empirical antibiotics. The co-primary outcomes of the RCT are the incidence of culture-proven EOS (non-inferiority) and unnecessary antibiotics administration (superiority). The required sample size for the RCT is 900 patients. Infants with a high- or low-risk of EOS are excluded from randomization but included in a concurrent observational study and treated according to the Dutch EOS guideline. The primary outcome of this part is the diagnostic accuracy of presepsin.

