### Intervention description {11a}

Infants at moderate risk of EOS will be randomly assigned (1:1 ratio) to the intervention or comparator arm. In the intervention arm, empirical antibiotics will only be started when the presepsin level is ≥ 645 pg/ml [14]. The result of the presepsin test will be communicated with the attending physicians as positive or negative without mentioning the exact level. Infants allocated to the comparator arm and those who will not be randomized will be treated according to standard care following the Dutch EOS guideline, with the treating physician and research team blinded to the presepsin test result.

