### Sample size {14}

Incidence of culture-proven EOS is assumed to be 1.4% based on the most recent and largest cohort with identical GA (< 32 weeks, *N* = 43,178) [4] and confirmed by screening 4 years admission data (2016–2019) of the NICU of Erasmus MC (Rotterdam, The Netherlands). With a plasma presepsin cutoff of 645 pg/ml, sensitivity is 100% (95% CI 78–100%) and specificity is 54% (95% CI 41–62%) for detecting EOS [14]. To balance the feasibility and the safety of the study, we have chosen a non-inferiority margin of 2% for the absolute between-RCT-arms difference in culture-proven EOS incidence (intervention–control) [24]. We deem this extra absolute risk acceptable in light of the incremental daily increased risk of adverse events with administration of antibiotics (NEC, LOS, death) [7]. Assuming there is no difference in culture-proven EOS between both study groups, a sample size of 427 is needed in both study groups (total *N* = 854), using a two-group, large-sample normal approximation test of proportions with 80% power and 1-sided 5% significance level. For the co-primary superiority outcome unnecessary antibiotics prescription < 72 h after birth, it is estimated that approximately 70% of all infants in the control group will discontinue antibiotics within 72 h (ref). Based on expert opinion, we consider an absolute reduction of 30% or more clinically relevant. Based on the aforementioned diagnostic accuracy of a presepsin cut-off level of 645 pg/ml, with a number of 427 in both study groups, we expect to detect a 30% reduction in the co-primary superiority outcome with a power of 99% and a 2-sided alpha of 0.05 (two-group Fisher’s-exact test). To allow for some unassessable cases (e.g. based on technical issues or withdrawn consent, estimated at 5%), a number of 450 will be included in both RCT-arms. The total study population is estimated to consist of 20% low risk (*N* = 244), 70% moderate risk (*N* = 900), and 10% high risk infants (*n* = 122).

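### The only split of clinical outcomes by presepsin that the protocol names is made inside the intervention arm; a between-arm comparison below 645 pg/ml would be randomised and should be named

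*Protocol article*

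**What the plan says.** **Where the arms differ.** Intervention description {11a} states: "In the intervention arm, empirical antibiotics will only be started when the presepsin level is ≥ 645 pg/ml". For the comparator arm, the abstract's Methods state that "infants will be treated according to the standard of care following the Dutch EOS guideline, equivalent to starting empirical antibiotics". So the rule for starting antibiotics separates the arms only below the cut-off.

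**Presepsin is available in both arms.** The abstract's Methods state: "Presepsin levels are determined from umbilical cord blood or during the first regular blood draw in all infants born" below 32 weeks. Comparator infants are managed "with the treating physician and research team blinded to the presepsin test result". In the intervention arm the result is "communicated with the attending physicians as positive or negative without mentioning the exact level".

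**Planned analyses.** Statistical methods {20a} compares whole arms by intention to treat, with a per-protocol analysis added for EOS. Methods for additional analyses {20b} states: "Subgroup analyses are planned for GA 24–28 weeks versus 28–32 weeks and SGA patients". Its next sentence defers subgroup and other additional analyses to a statistical analysis plan, due before database lock.

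**The presepsin split that is named.** Interim analyses {21b} sets a mortality warning at halfway: 10% assumed in controls against more than 15% in the intervention arm. If it is met, the intervention group is to be inspected to see whether the excess lies with the presepsin-low infants, the presepsin-high infants, or both. No comparison with presepsin-low controls is mentioned.

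**The concern.** Infants at or above 645 pg/ml are meant to start antibiotics in either arm, so they add little to a contrast between withholding and giving. Any harm or benefit of withholding arises below the cut-off and is averaged over the whole arm.

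The interim inspection turns to presepsin exactly when the committee must judge whether withholding caused excess deaths. It then looks at low and high infants within one arm. Those groups are defined by an infection marker, so their prognosis may differ whatever the treatment. The randomised reference group, comparator infants below 645 pg/ml, is already sampled but not named. At stake are a stopping recommendation that could rest on a confounded contrast, and less sensitive supportive evidence at the end on mortality and on NEC, LOS or death.

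**Working it through.** **1. The plan's own figures reproduce.** Non-inferiority with 1.4% in both arms, margin 2%, one-sided 5%, 80% power:
(1.645 + 0.842)² × 2 × 0.014 × 0.986 / 0.02² = 427 per arm. Then 427 / 0.95 gives 450 per arm. For superiority, 70% v 40% with 427 per arm has power above 99%, as stated.

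**2. Share of infants below the cut-off.** Sample size {14} states: "With a plasma presepsin cutoff of 645 pg/ml, sensitivity is 100% (95% CI 78–100%) and specificity is 54% (95% CI 41–62%) for detecting EOS". With EOS incidence p = 1.4%:
f = (1 − p) × specificity + p × (1 − sensitivity)
- Point estimates: 0.986 × 0.54 + 0.014 × 0 = 0.532.
- Lowest (specificity 41%, sensitivity 100%): 0.404.
- Highest (specificity 62%, sensitivity 78%): 0.614.

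That is 0.532 × 450 = 240 infants per arm (182–276), or 227 of 427. At the interim it is 0.532 × 225 = 120 per arm.

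**3. Size of the dilution.** Whole-arm difference = f × (difference below) + (1 − f) × (difference at or above). If the second term is zero, the whole-arm difference is 0.53 of the difference below the cut-off (0.40–0.61). The 5-point mortality signal then corresponds to 5 / 0.532 = 9.4 points below 645 pg/ml (8.1–12.4).

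**4. Why the within-arm split cannot attribute the excess.** Let mL and mH be mortality in low and high infants when all are treated, and d the effect of withholding.
- Low minus high inside the intervention arm: (mL + d) − mH = d + (mL − mH). The last term cannot be estimated from that arm.
- Low v low between arms: (mL + d) − mL = d.

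Take the protocol's signal, 10% v 15%, with all of the excess in low infants (d = 9.4 points). The within-arm contrast vanishes if mH − mL is also 9.4 points:

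| | Below 645 | At or above 645 | Whole arm |
|---|---|---|---|
| Comparator | 5.6% | 15.0% | 10% |
| Intervention | 15.0% | 15.0% | 15% |

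(mL = 10 − 0.468 × 9.39 = 5.6; mH = 5.6 + 9.4 = 15.0.) The planned inspection would see 15% in both groups, although every excess death is in the low group. With equal prognosis (10% in both strata) it would see 19.4% v 10% and be right, but the intervention arm alone cannot show which case applies.

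**5. Sensitivity gained.** With equal baseline risk in both strata, the expected z-statistic below the cut-off is 1/√0.532 = 1.37 times the whole-arm one (1.28–1.57). As an illustration, assume a 20% control event rate in both strata and a 10-point benefit below the cut-off (two-sided 5%). Power is then 54% with whole arms (427 per arm, difference 5.3 points) and 85% below the cut-off (227 per arm). With a 30% rate and a relative risk of 0.75 it is 25% v 45%; with a 25% rate, 21% v 37%. These event rates and effects are assumptions, not protocol figures.

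**6. Precision.** At 10% mortality in both arms, the 95% half-width below the cut-off is 1.96 × √(2 × 0.10 × 0.90 / 120) = 7.6 points at the interim, and 5.4 points with 240 per arm.

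**7. EOS below the cut-off.** Expected cases per arm: 450 × 0.014 × (1 − sensitivity) = 0 at 100% sensitivity and 1.4 at 78%.

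**The case against.** **The list may not be complete, and the plan defers.** A reader might infer from the GA and SGA sentence that presepsin strata have been ruled out. The next sentence of {20b} leaves further analyses to an analysis plan that is not shown, so absence from that list is not an error. The objection has less force for {21b}. That inspection happens halfway, the analysis plan is due only before database lock, and the protocol itself describes the split. Its list of items is not exhaustive, however, and the committee could still ask for the comparator data.

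**Whole-arm intention-to-treat answers the stated question.** Objectives {7} asks about adding a presepsin-guided decision, which is a strategy. A reader might conclude that dilution makes the EOS test too lenient, since 2% over the whole arm equals 2 / 0.532 = 3.8% below the cut-off. The documents do not support calling this a bias: the margin was set on the between-arm scale, and the whole-arm contrast estimates that quantity without bias.

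**Not every contrast suffers.** The 30-point superiority target is a whole-arm figure. The expected whole-arm reduction is about 70% × 54% = 38 points (29–43). Nothing of consequence is lost there.

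**The stratum says little about EOS.** This stands: 0 to 1 cases per arm cannot carry an inferential comparison.

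**A zero difference at or above 645 pg/ml is not assured.** This stands too. Allocation is open, and a positive result is disclosed in one arm and hidden in the other, so later care could differ. It is a reason to report that stratum, not to leave both out.

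**Conclusion.** The point holds as an inexpensive improvement, not as a fault in the primary analysis. About 53% of randomised infants (40–61%) lie where the start of antibiotics differs between arms, so whole-arm absolute differences in mortality and in NEC, LOS or death are about half of those in the infants affected. The named interim split is confined to one arm, is not randomised, and cannot attribute excess mortality to withholding.

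The share rests on the protocol's incidence, sensitivity and specificity applying to the moderate-risk infants. The halving assumes the same care in both arms at or above the cut-off; the 1.37 ratio also assumes equal baseline risk in the strata. The stratum comparison is randomised provided presepsin is sampled alike in both arms and before antibiotics. The documents do not support the wider readings that the non-inferiority conclusion is biased or that the superiority result is weakened.

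**What to change.** - **Interim analyses {21b}:** replace the intervention-only inspection with two between-arm comparisons of mortality, each with a confidence interval: infants below 645 pg/ml, and infants at or above it. Composition of the data monitoring committee {21a} already gives the committee unblinded access, so its statistician can do this without informing the trial team.
- **Methods for additional analyses {20b}:** prespecify, as supportive to the whole-arm intention-to-treat analysis, the between-arm difference with confidence interval below 645 pg/ml for mortality, sepsis-related mortality, and NEC, LOS or death. Show EOS in that stratum descriptively, and the stratum at or above 645 pg/ml as a check.

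The cost is a short amendment and one extra table, with no new data. Intervals will be wide at about 230–240 infants per arm and wider at about 120 at the interim. Comparator presepsin results must stay hidden from the trial team until database lock.

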### Methods in analysis to handle protocol non-adherence and any statistical methods to handle missing data {20c}

Analyses will be performed using the intention-to-treat principle and also using the per-protocol principle for the co-primary non-inferiority outcome to evaluate the consistency of both analysis approaches compliant with recommendations for non-inferiority analyses [25]. The per-protocol population will exclude patients with major protocol deviations, which may have an impact on the evaluation of the co-primary non-inferiority outcome; these will be defined in the statistical analysis plan before the database lock.

No missing data for the primary outcome are expected and therefore methods such as imputation are not anticipated.

### Plans to give access to the full protocol, participant level-data and statistical code {31c}

Metadata will be published on Amsterdam UMC DataverseNL after publication at the end of this research project. All data generated during the study, including participant-level data and statistical code, are available upon reasonable request with the corresponding author.

## Oversight and monitoring

### Composition of the coordinating centre and trial steering committee {5d}

The trial steering committee (TSC) includes the principal investigator of each participating centre, two additional investigators from the coordinating centre, and N3 representatives. The TSC has scientific responsibility for the study and is the main decision-making body of the study. Furthermore, overall supervision of the study will be provided by the TSC.

### Composition of the data monitoring committee, its role and reporting structure {21a}

An independent DMC, consisting of a statistician, pediatric infectious disease specialist, neonatologist, and representative of the patient and parent organization Care4Neo, forms the DMC. The DMC will have access to unblinded study data to allow for interim data analyses. The DMC will make their final recommendations regarding the results of interim data analysis and may recommend early trial termination with unanticipated safety concerns (see paragraph "Interim analyses {21b}"). They may also recommend cessation of the trial if it is unable to successfully recruit participants, encounters improper data handling, or is not able to successfully implement study protocols.

The advice(s) of the DSMB will only be sent to the principal investigator of the study. Should the principal investigator decide not to fully implement the advice of the DSMB, the principal investigator will send the advice to the reviewing MERC, including a note to substantiate why (part of) the advice of the DSMB will not be followed.

### Adverse event reporting and harms {22}

Serious adverse events (SAEs) will be reported through the web portal *Onderzoeksportaal* from the Central Committee on Research Involving Human Subjects (CCMO) to the accredited MREC within 7 days of first knowledge. These SAEs are defined as sepsis-related mortality and start of antibiotic therapy in patients that were initially not started on antibiotics in the presepsin-guided therapy intervention arm. This study population (critically ill preterm infants) has a high risk of other serious complications (so-called “context-specific SAE’s”), which are inherent to their vulnerable condition and unrelated to the intervention that is under evaluation in this trial. These complications are included in the primary and secondary outcomes of this study and are recorded in the Case Report Form. This documentation will include the date of diagnosis, classification/gradation of the complication, type of action taken if appropriate (with some complications a wait and see approach is warranted). In light of the above, immediate and individual reporting of all these condition-related complications will not enhance the safety of the study. Once a year, an overview of the aforementioned complications for each treatment arm and ordered by organ system will be presented to the DMC and MREC.

### Frequency and plans for auditing trial conduct {23}

The study will be monitored by clinical research associates employed by certified monitor organizations and by means of personal visits to investigator’s facilities and other communications (e.g. telephone calls and written correspondence). The visits will be conducted depending on a prespecified number of included study subjects and comprises review of informed consent procedures, source data review and verification, study protocol adherence, adherence to GCP and applicable national regulations. All monitoring agreements and activities are specified in a separate monitoring plan.

